### Haemoglobin levels at birth and outcomes

Factors such as low haematocrit, mean blood pressure, urine output and high oxygen requirement during the first 24 hours of life have been shown to influence short term outcomes for infants(18). Research by Banerjee et al has shown that low haemoglobin at birth is an independent risk factor for mortality and probability of receiving blood transfusion in preterm infants at<32 weeks gestation. Improving infants blood volume and haemoglobin level at birth may reduce mortality and short term complications of prematurity(19).

One of the goals of improving essential neonatal care is to deliver adequate oxygen to meet tissue demand. Increasing fetal haemoglobin by placental transfusion is an extremely effective method of enhancing arterial oxygen content, increasing cardiac output and improving oxygen delivery(20). Oxygen delivery is dependent upon cardiac output, haemoglobin concentration oxygen carrying capacity of haemoglobin and arterial oxygen saturation. Anaemic preterm infants may be less able to maintain oxygen delivery.

### Placental transfusion

Placental transfusion is the transfer of residual placental blood to the baby during the first few minutes of age. The goal of placental transfusion is to facilitate transfer of blood volume from placenta to the newborn.

The fetus has an approximate blood volume of 70ml/kg and the placenta a further 45ml for each kg of fetal weight. If the umbilical cord is not clamped immediately after birth a volume of 20-35ml/kg can be transfused to the fetus potentially representing 50% increase in fetal blood volume(21).Two placental transfusion techniques are umbilical cord milking and delayed cord clamping.

### Umbilical cord milking

A recent systematic review and meta-analysis of 7 randomized clinical trials of umbilical cord milking in infants delivered at <33 weeks demonstrated that infants that undergo umbilical cord milking have higher haemoglobin and lower risk of oxygen requirement and intraventricular haemorrhage of all grades compared with immediate cord clamping(22). Another meta-analysis by Dang D et al showed that by facilitating the early stabilization of blood pressure, UCM at preterm birth was found to be comparatively safe and associated with lower blood transfusion exposure and lower incidence of IVH, NEC and death(23).

A study done by kateria et al showed that umbilical cord milking produced greater placental transfusion, demonstrated by higher initial haemoglobin, higher blood pressure and improved systolic blood flow and urine output for infants delivered by caesarean delivery(24).

Cord milking before clamping improves pulmonary blood flow immediately at birth and assists lung expansion at the onset of respirations. Milking assisted with earlier onset of breathing compared with delayed cord clamping(20). Cord milking may offer an advantage over delayed cord clamping in neonates who are considered too unstable to wait for delayed cord clamping and are at higher risk for intraventricular haemorrhage or death.

Umbilical cord milking can be performed in any low resource setting and provides adequate placental transfusion without delay making it feasible for infants requiring immediate resuscitation. It is an easy intervention with potential to improve neonatal outcome. Milking the cord increases the initial haematocrit and may lessen the need for transfusion in the neonatal period(25).

One published randomized clinical trial has compared umbilical cord milking with immediate cord clamping in extremely preterm deliveries(less than 28 weeks) showed that umbilical cord milking reduced the need for red blood cell transfusions in the neonatal period, increased infants blood pressure in the first 12 hours of life and urine output in the first 72 hours of life(26).

### Delayed cord clamping

The American college of obstetrician and gynaecologists recommend delay cord clamping in healthy infants for 30-60seconds. Benefits in the preterm infants include improved transitional circulation, better establishment of red cell volume, decreased need for blood transfusion and lower incidence of necrotizing enterocolitis and intraventricular haemorrhage(27,28). WHO recommends umbilical cord not to be clamped earlier than one minute after birth in term and pre-term infants(29). The American academy of paediatricians recommends delayed cord clamping for at least 30-60 seconds for term and preterm infants(30).

In a large clinical trial that compared delayed cord clamping with neonatal venous haematocrit levels and clinical outcome at term, it was found that prevalence of haematocrit(<45%)anaemia was lower in groups assigned cord clamping at 1 minute and 3 minutes compared to 15 seconds. The intervention seemed to reduce the rate of neonatal anaemia(31).

Delayed cord clamping allows for expansion of blood volume from autologous placental blood to provide 60% more red blood cells and 30% more blood volume than immediate cord clamping. For preterm neonates this translates to better cardiopulmonary adaptation to extra uterine life and diminished need for red cell transfusions(32).

### Risks and benefits

The greatest barriers to clinical application of placental transfusion are theoretical risks such as over transfusion, symptomatic polycythemia, jaundice, hypothermia and delayed resuscitation. None of these risks have appeared in the current randomized controlled trials and meta-analysis on term or preterm infants (20,33,34).

Too many red blood cells has been a concern but red cells and blood volume expand together, increasing capillary beds throughout the body(35).

Recent meta analysis shows no difference in clinical jaundice(34). There was a slight increase in the need for phototherapy in delayed cord clamping(2%) but recent evidence that higher levels of bilirubin within normal limits may offer neuroprotection(36).

In a study by Rabe H et al, a prospective cohort study, showed milking of the cord 4 times did not have any long-term adverse effect on neurodevelopmental outcome, suggesting that cord milking could be used as an alternative to delayed cord clamping(37)

Many maternity care providers continue to clamp the umbilical cord immediately after an uncomplicated vaginal birth, even though the significant benefits of DCC are now well known. In some cases this continued practice is due to a misunderstanding of placental physiology in the first few minutes after birth. In others, human nature plays a role: we are often reluctant to change the way we are taught to do things, even in the face of clear evidence. Though there is no scientific support for ICC, entrenched medical habits can be glacially slow in changing. Often heard objections are that immediate cord clamping helps prevent post partum haemorrhage but there is no convincing evidence to support this.

Studies have shown no increase in the incidence of postpartum haemorrhage from delayed umbilical cord clamping(34). Concerns regarding maternal risks become particularly relevant in high risk pregnancy in which the benefits of DCC need to be balanced with the timely resuscitation of the woman such as in cases of haemorrhage from placenta previa or placental abruption after delivery of an infant.

# CONCEPTUAL FRAMEWORK

Premature Neonates

(28-36weeks and 6 days)

PREDISPOSED TO ANAEMIA

1. Inadequate red blood cell production.
2. Shortened red blood cell life span.
3. Iron deletion impairing recovery from anaemia.

METHODS TO INCREASE PLACENTAL TRANSFER

UMBILICAL CORD MILKING

DELAYED CORD CLAMPING

- Active placental transfer of cord blood.
- Takes 20 seconds.
- Improves circulatory volume at birth
- Higher systemic blood pressure in neonates improving oxygenation.
- Higher red blood cell levels
- Passive placental transfer of cord blood.
- Between 1-3 minutes
- Improves circulatory volume at birth.
- Increases oxygen carrying capacity to tissues
- Improves iron statues up to 6months.

- Increased Haemoglobin
- Increased Haematocrit
- Decreased Neonatal Anaemia
- Decreased post partum haemorrhage
- Decreased jaundice

Figure 1: Conceptual Framework

# Conceptual framework narrative

Developmentally determined physiological processes predispose the premature neonate directly to anaemia. These factors are inadequate red blood cell production, shortened red blood cell life span and iron depletion impairing recovery from anaemia.

The placenta is a subsidiary reservoir of fetal blood that could prove useful to the predisposed neonate. Placental transfusion is a useful strategy that can be used to increase placental transfer of vital nutrients to the neonate. Two such strategies that can be employed to increase of placental transfusion are umbilical cord milking and delayed cord clamping.

Both strategies have similarities in the physiological processes that aim to be beneficial to the neonate except that delayed cord clamping is a passive process and takes place over 1-3 minutes whereas umbilical cord milking is through active placental transfer and takes approximately 20 seconds.

The study seeks to compare selected haematological and clinical outcomes from both strategies. Umbilical cord milking may replicate or increase benefits by two fold amongst preterm neonates compared to delay cord clamping.

# Justification

Neonatal mortality is the leading cause of mortality in children under the age of five years in Kenya. Nearly 35% of under-5 deaths occurred during the neonatal period; 1/3^rd^ of all neonatal deaths are due to severe infections, followed by birth asphyxia, preterm births and congenital anomalies.

Preterm neonates are at risk of developing complications that will affect their chances of survival. The extent to which they develop complications strongly depends on the quality of care they receive at birth. In a preterm neonate already predisposed to such disadvantages the extra blood received from the placenta can give a boost to their already disadvantaged status.

The additional blood obtained through placental transfer can improve haemoglobin levels at birth, stabilize neonatal transition, reduce rates of blood transfusion and increase neonatal iron storage in preterm neonates.

Delayed cord clamping is recommended by all major obstetric societies but less information exists on umbilical cord milking.UCM is potentially an effective, faster placental transfer strategy when DCC cannot be performed such as when a neonate requires resuscitation or to expedite delivery in the advent of maternal complications.

Directly comparing the recently recommended practice of delayed cord clamping to umbilical cord milking before clamping has potential to prove beneficial for the neonates in question, as well inform obstetric practice and policy on placental transfusion in a maternity with heavy workloads.

If this study shows that umbilical cord milking has the same benefits if not more to the preterm neonate, this can give clinicians confidence to implement and use umbilical cord milking as part of their management plan for preterm neonates in a maternity with a high turnover of patients. It can also be used to advocate for policies to introduce umbilical cord milking as a routine practice to be done on all preterm neonates. Currently no specific protocol with regards to placental transfusion exists in Kenyatta national hospital.

Most studies have been done in the developed countries; this study seeks to replicate similar or better outcomes for haemoglobin levels amongst a population with higher incidence of anaemia.

# Study objectives

Research question:

Is there a difference in haemoglobin, haematocrit and neonatal jaundice between preterm infants who will undergo umbilical cord milking versus delayed cord clamping?

Broad objective:

To determine the effects of umbilical cord milking versus delayed cord clamping on haemoglobin, haematocrit, and neonatal jaundice of preterm neonates.

Primary objectives:

Among preterm neonates at 28-36 weeks who will undergo umbilical cord milking versus delayed cord clamping at vaginal or caesarean delivery, to:

1. Determine and compare the mean haemoglobin and haematocrit values at 24 hours of life.

Null hypothesis: There is no difference in the mean haemoglobin and haematocrit values 24 hours after birth comparing pre term neonates delivered at 28-36 weeks who will undergo umbilical cord milking versus delayed cord clamping.

1. Determine and compare the incidence rate of neonatal polycythemia at 24 hours of life.

Null hypothesis: There is no difference in the incidence rate of neonatal polycythemia at 24 hours after birth comparing pre term neonates delivered at 28-36 weeks who will undergo umbilical cord milking versus delayed cord clamping.

1. Determine and compare the incidence rate of neonatal jaundice within the first week of life.

Null hypothesis: There is no difference in the incidence rate of neonatal jaundice within the first week of life comparing pre term neonates delivered at 28-36 weeks who will undergo umbilical cord milking versus delayed cord clamping.

Secondary objectives:

Among preterm neonates at 28-36 weeks who will undergo umbilical cord milking versus delayed cord clamping at vaginal or caesarean delivery, to:

1. Determine and compare the incidence rate of neonatal anaemia within the first 24 hours of life.
2. Determine and compare the incidence rate of maternal primary post partum haemorrhage within 24 hours of delivery.

# RESEARCH METHODOLOGY

### STUDY DESIGN

Single blind, open-label, Randomised controlled trial.

This will be a parallel group study with 1:1 randomisation. Application of block randomization will be used with 140 participants in each arm comparing neonatal venous haemoglobin and haematocrit values between umbilical cord milking and delayed cord clamping among preterm babies delivered at Kenyatta National Hospital, Nairobi 24 hours after birth.

### STUDY LOCATION:

This study will be carried out at the Kenyatta National Hospital (KNH) labour ward, maternity theatres, post natal wards and the neonatal intensive care unit. The KNH is the largest teaching and referral hospital in East and Central Africa and within its complex are College of Health Sciences (University of Nairobi); the Kenya Medical Training College; Kenya Medical Research Institute and National Laboratory Service (Ministry of Health).

KNH has 50 wards, 22 out-patient clinics, 24 theaters (16 specialized) and Accident & Emergency Department. Out of the total bed capacity of 2,009,196 of the beds are for obstetric services. It is located in the Upperhill area of the capital city of Kenya, Nairobi in Nairobi County and serves the lower and middle class population.

### STUDY PERIOD

This study will be carried out at Kenyatta National hospital from December 2017 to June 2018.

### STUDY POPULATION:

**INCLUSION CRITERIA**:

This will include:

- Mother-baby pairs between 28 to <37 weeks gestational age. Gestational age will be confirmed by use of Last Menstrual Period dating or if available a first trimester ultrasound scan will be used. After delivery a Ballard score will be done by the paediatrician at 24 hours of life to validate the gestational age.
- Preterm deliveries occurring for both elective indications and spontaneously through either vertex delivery or caesarean section.
- Reassuring fetal status.
- Informed consent must be provided.

**EXCLUSION CRITERIA**:

- Pregnant women with multiple gestations.
- Neonates with congenital abnormalities(e.g. neural tube defects)
- Red cell isoimmunisation.
- Seropositive serology for HIV and VDRL.
- Ante partum haemorrhage including Placenta accrete or placenta abruption.
- Need for neonatal resuscitation.
- Tight nuchal cord necessitating early cutting.
- Patients who are incapable of informed consent (severely ill), or unwilling to undergo randomization.

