**Analysis plan**: Levels of haemoglobin and haematocrit of newborn infants following umbilical cord milking will be compared to those of newborns who undergo delayed cord clamping using unpaired students T- test and a P value <0.05 for significance. Prevalence will be compared using proportions and chi squared test of independence. Measurements of excess risk will be estimated using relative risk at 95%confidence interval that excludes the null value will be considered significant. Intention to treat analysis will be used.

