### Randomization

Randomization will be done by the midwives carrying out the interventions who are part of the study in labour ward. Randomization will be done when delivery is imminent. This is characterised by urge to bear down or second stage of labour. For caesarean delivery randomization will be done at induction of anaesthesia in the operating theatre.

The statistician will use block randomization in equal blocks of 14 until the total sample size is achieved. They will be randomized into two groups. A random allocation sequence will be done on computer generated slips of paper bearing the allocation code which will be kept in serially numbered opaque sealed envelopes with an unpredictable allocation code. Recruited patients will be randomly assigned to either the control arm or the intervention arm in a 1:1 ratio.

Using STATA statistical package randomization ado package, computer generated random sequences in blocks of 4 and 6 will be used to determine the order of intervention allocation and avoid anticipation of the allocation group for the next patient while maintain a balance of the patients recruited in each of the arms at each point. The randomly generated list of the allocation sequence will be printed on small cards each representing the allocation of each patient in the order generated by the software. Each of these cards will be sealed in opaque envelopes that will be sequentially numbered in the order of the list generated.

After identifying an eligible patient and consent granted the next sequentially numbered envelope will be opened and then will determine which arm the patient will be allocated. Each participant will be assigned a unique 4 digit number for subject identity and confidentiality.

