### Blinding

The nature of the intervention makes it impossible to blind the clinicians performing the intervention. Although study staff will not inform the mothers of their allocation, the nature of the intervention makes it impossible to blind them. If an already randomized mother later becomes ineligible, the assigned allocation code will not be re-used. The principle investigator or the research assistants will monitor the delivery and therefore will not be blinded to treatment assignment.

The laboratory staff performing analysis of blood samples will be blinded to the allocation group.

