### Intervention groups:

A structured survey questionnaire will be used to gather obstetrical and medical details from mothers that meet study criteria during the first stage of labour. The questionnaire will be filled in by the research assistants or principal investigator. Once delivery is imminent, the midwife will immediately open a sealed, numbered, opaque envelope containing the treatment allocation. Neonates will undergo either umbilical cord milking or delayed cord clamping.

For neonates undergoing UCM, after delivery the cord will be pinched as close to the placenta as possible and milked towards the infant over 2 second duration. The cord is then released and allowed to refill over 1 to 2 seconds between each milking motion. This is repeated a total of 4 times. After milking the cord will be clamped and handed over to the neonatal receiving team.

For neonates undergoing DCC, the cord will be clamped after waiting 60 seconds. Timing will be noted by using a stop watch timer in the labour ward delivery room and a wall mounted clock in the maternity theatre.

The position of the new born during DCC or UCM will be on the maternal abdomen for both caesarean delivery as well as after spontaneous vaginal delivery.

Early care of the new born should be initiated, including drying and stimulating for first breath or cry. Maintain normal temperature with skin to skin contact and covering the infant with dry linen. Secretions should be cleared if only copious or appear to be obstructing the airway.

DCC and UCM should not interfere with active management of third stage of labour including Uterotonics agents after delivery of the newborn to minimize bleeding.

If placental circulation is not intact, such as in the case of placental abruption, abnormal placentation, and cord avulsion as well as Newborns without spontaneous breathing during the first 10 seconds of life, with major congenital malformations diagnosed at birth and with tight nuchal cord will be subjected to early cord clamping based on need for resuscitation, regardless of the assigned intervention.

Clinicians and midwives involved in the delivery will be trained on the process of UCM by live clinical tutorials and videos.

All patients irrespective of which group they are in will be reviewed by consultants and senior house officers during the ward rounds.

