### DATA VARIABLES

- Primary dependent variables; the infants’ venous haemoglobin and haematocrit value will be measured at 24 hours of life. Polycythemia, Neonatal jaundice and need for phototherapy/exchange transfusion
- Secondary dependent variables: neonatal anaemia, maternal primary post partum haemorrhage.
- Independent variables: Delayed cord clamping (control) and Umbilical cord milking (intervention).

#

[figure not shown]

Excluded (n= )

- Multiple gestation (n= )
- Declined consent (n= )
- Major congenital abnormalities (n= )
- Red cell isoimmunisation(n= )
- Positive serology HIV/Hep/VDRL (n= )
- Tight nuchal cord (n= )
- Ante partum haemorrhage (n= )
- Need for neonatal resuscitation (n= )

Assessed for eligibility (n= )

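### Some exclusion criteria can be settled only at or after birth, when the pair is already randomised, and the protocol conflicts on whether those pairs are analysed

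*Protocol*

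**What the plan says.** **Timing of allocation.** Protocol, Randomization: "Randomization will be done when delivery is imminent". For caesarean births: "For caesarean delivery randomization will be done at induction of anaesthesia in the operating theatre". Intervention groups agrees that the midwife opens the envelope before the birth. Consent words the timing more loosely, but these two sections settle it.

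**Exclusions.** Exclusion Criteria lists "Need for neonatal resuscitation", tight nuchal cord and congenital abnormality. The screening form in Appendix II repeats all three. The text of the flow diagram (Figure 2) puts them in the list of exclusions that goes with eligibility assessment.

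**The same infants elsewhere.** Under Intervention groups, infants who are not breathing by 10 seconds, have a malformation found at birth or have a tight nuchal cord "will be subjected to early cord clamping based on need for resuscitation, regardless of the assigned intervention". Dummy Table 2 counts need for resuscitation by arm, as a baseline characteristic.

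**Later ineligibility.** Blinding: "If an already randomized mother later becomes ineligible, the assigned allocation code will not be re-used". It does not say whether the pair stays in the analysis. The flow diagram has a line in each arm for exclusions from analysis.

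**Analysis principle.** Abstract, analysis plan: "Intention to treat analysis will be used".

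**Who judges, and the premise on breathing.** Blinding states that those who perform the intervention, and the study staff who monitor the delivery, know the arm. The literature review on cord milking states "Milking assisted with earlier onset of breathing compared with delayed cord clamping(20" (the closing figure is a citation number).

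**The concern.** A criterion that cannot be known when the envelope is opened cannot act as an eligibility criterion. Applied at birth, it removes a pair that has already been randomised. Two things are then at stake.

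- **If these infants are removed,** staff who know the arm decide who is analysed. Infants who need resuscitation may well differ in haemoglobin from the rest. If the arms lose different numbers of them, the comparison is no longer the randomised one.
- **If they are kept,** as intention to treat requires, some infants in both arms receive neither milking nor delayed clamping. The contrast is diluted, and the sample size makes no allowance for that; its 10% is for attrition only.

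The choice also affects credibility. Appendix IV has an unblinded statistician monitoring the data continuously, so a choice left open now could later be made with the arm results in view.

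**Working it through.** **1. The passages side by side**

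| Reading | Sections that fit it |
|---|---|
| Infants leave the trial | Exclusion Criteria; Appendix II; flow diagram (exclusions at eligibility) |
| Infants stay, in their arm | Intervention groups (clamped early whatever the allocation); Table 2; Abstract (intention to treat) |
| Undecided | Blinding (code not re-used); flow diagram (generic line for exclusions from analysis) |

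No section decides between the two readings.

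**2. The plan's own figure**

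Inputs from Sample Size: SD 2, difference 0.7, z values 0.84 and 1.96, ratio 1:1.

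n = 2 × 2² × (0.84 + 1.96)² / 0.7² = 8 × 7.84 / 0.49 = 128 per arm, as stated. Adding 10%: 256 × 1.10 = 281.6, stated as 280, or 140 per arm. If 10% of those are lost, 140 × 0.90 = 126 per arm remain.

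**3. If the infants are removed: possible shift**

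The documents give no rate, so every input here is assumed. Suppose there is no true effect, a share s of infants are slow starters with haemoglobin lower by D, and only slow starters are excluded, at shares e(UCM) and e(DCC) of all randomised infants. The mean of an analysed arm is then lower by D × (s − e)/(1 − e), and the shift is the difference between the arms.

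| s | D (g/dl) | e(UCM) | e(DCC) | Shift, UCM − DCC (g/dl) |
|---|---|---|---|---|
| any | any | equal | equal | 0 |
| 5% | 1 | 2.5% | 5% | −1 × 0.025/0.975 = −0.03 |
| 15% | 1.5 | 13.5% | 15% | −1.5 × 0.015/0.865 = −0.03 |
| 15% | 1.5 | 12% | 15% | −1.5 × 0.03/0.88 = −0.05 |
| 15% | 1.5 | 7.5% | 15% | −1.5 × 0.075/0.925 = −0.12 |
| 20% | 2 | 10% | 20% | −2 × 0.10/0.90 = −0.22 |

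In the last row 126 and 112 infants remain. The standard error is 2 × √(1/126 + 1/112) = 0.26, and the two-sided type I error is 13.7% instead of 5%. The sign, against milking, follows from assuming that more infants are excluded under delayed clamping.

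**4. If the infants are kept: dilution**

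Assume that a share q of both arms is clamped early and shows no arm difference. The expected difference becomes 0.7 × (1 − q). Power is for a two-sided 5% t-test with SD 2.

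| q | Difference | 140 per arm | 126 per arm |
|---|---|---|---|
| 0% | 0.700 | 83% | 79% |
| 5% | 0.665 | 79% | 75% |
| 10% | 0.630 | 75% | 70% |
| 15% | 0.595 | 70% | 65% |
| 20% | 0.560 | 65% | 60% |

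The first row separates ordinary attrition (83% to 79%) from dilution (the fall down each column).

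**The case against.** **No section says these infants are dropped.** A reader might infer that the protocol breaches its own intention-to-treat promise. The documents do not support that: the intervention section and Table 2 fit keeping the infants, not re-using an allocation code is sound practice, and the exclusions line in the flow diagram is a generic reporting item. This stands, so the defect is an unreconciled contradiction. The detail of analysis sets may also lie in a statistical analysis plan that is not shown. But eligibility, the timing of randomisation and the flow diagram belong to the protocol, and the conflict is there.

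**Allocation can hardly affect all three criteria.** A reader might infer that it drives every one of them. It cannot cause a malformation or a nuchal cord; the remaining risk there is unblinded judgement of what counts as tight, or selective removal. Some malformations are also known before birth and can properly be excluded then. This stands.

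**Even for resuscitation the route may be narrow.** Four strokes of 2 seconds with three refills of 1 to 2 seconds take 8 + 3 to 8 + 6, or 11 to 14 seconds, and the conceptual framework gives 20. Milking is therefore unfinished at the 10-second mark that triggers early clamping, and the sentence on earlier breathing gives no time scale. This weakens the route without closing it, because the exclusion criterion itself carries no time limit and is judged by staff who know the arm.

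**The figures are hypothetical.** This also stands. The larger shifts need strong assumptions, and milder ones give 0.03 to 0.05 g/dl. If the infants were dropped equally and were the only loss, power would still be 81% at 5% and 79% at 10%.

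**Conclusion.** The point holds in this form. Allocation is opened before birth, some listed exclusions are settled only at or after birth, and the protocol conflicts on whether the randomised pairs concerned are analysed. Applying the exclusions as written would remove randomised infants on unblinded judgement. For resuscitation need alone, the protocol's own premise makes it plausible that allocation affects who is removed.

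The size cannot be fixed from the documents. It runs from no shift to about 0.2 g/dl, roughly a third of the planned 0.7 (0.22/0.7 = 32%), and the upper end needs 20% slow starters with a 2 g/dl deficit, all excluded in one arm and half in the other. Keeping the infants avoids the bias at the price of power: 79% to 65% with 140 per arm, or 75% to 60% with 126, at 5% to 20% early clamping, if those infants show no arm difference.

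**What to change.** - Reconcile Exclusion Criteria, Appendix II and the flow diagram with Intervention groups, Table 2 and the intention-to-treat statement.
- Limit exclusion criteria to facts known when the envelope is opened. A malformation already diagnosed antenatally can remain as one.
- Analyse every randomised live-born infant with a 24-hour sample in the assigned arm, and record early clamping as non-adherence.
- Use a per-protocol or as-treated analysis only as a sensitivity analysis. Any removal of malformations found at birth belongs there too.
- Move the post-birth criteria out of the pre-randomisation box of the flow diagram. Report resuscitation, Apgar score and NICU admission as events after randomisation, not as baseline characteristics.
- State power as conditional on an assumed early-clamping share, with the basis for that share.

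**Cost.** The changes are to wording, the diagram and the tables. The stated power becomes somewhat less favourable. No extra patients are needed if that is accepted. To restore 80% under the dilution assumption, the size before attrition is 128.1/(1 − q)² (128.1 is the plan's formula with unrounded z values), or 142, 159, 178 and 201 per arm at 5%, 10%, 15% and 20%. The care rule for these newborns is not in question.
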